### Objectives of the CSC study

The primary objective of the CSC Study is to evaluate an innovative Internet-based prevention program for the prevention and reduction of substance use, anxiety and depressive symptoms, by combining the universal *CLIMATE Schools - Substance Use* program and the *CLIMATE Schools - Mental Health* program.

It is hypothesised that the CSC program will be more effective than; (1) school-based Health and Physical Education as usual, (2) the *CLIMATE Schools - Substance Use* program, and (3) the *CLIMATE Schools - Mental Health* program in relation to the following outcomes:

1) reducing the use and harmful use of alcohol and cannabis

2) reducing overall levels of anxiety and depression

3) increasing knowledge related to alcohol, cannabis anxiety and depression.

Secondary aims include examining the effects of the interventions on alcohol use related harms, self-efficacy to resist peer pressure, general disability, and truancy. The link between personality and substance use, as well as mental health will also be examined.

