### Sample size calculations

To account for cluster randomisation, sample size calculations were based on recent sample size requirements developed by Heo & Leon [49]. to detect intervention by time interactions in longitudinal cluster randomised clinical trials. The CSC trial will be powered to detect differences in the overall sample as well as between samples from each of four groups within the three States of NSW, QLD and WA. To allow for comparisons within each State, six schools (with at least 100 students) in each of the four intervention groups are required per state, giving a total of 24 schools per State (at least 2400 students). This achieves 80 per cent power to detect a standardized between-group mean difference of 0.15 (p = 0.05) in outcomes at the end of the trial with seven measurement occasions. An effect size of 0.15 is comparable to previous school-based trials of universal mental health and substance use prevention programs and would have substantial benefits on a population level based on recent economic modelling [50]. To account for school dropouts during the trial, which we expect to be approximately 10 per cent, we aim to recruit at least 28 schools in each State (at least 2800 students). This will result in an overall sample of 8400 students from 84 schools at baseline to test the efficacy of the CSC intervention in comparison to the other groups. Based on previous research using the *CLIMATE Schools* programs, school participation rates for similar trials were approximately 30 per cent [48,51]. Therefore, to recruit a total of 84 schools, approximately 270 schools will be approached to participate.

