#### ***Statistical analysis***

Single-level analyses; one-way analyses of variance (for normally distributed data), Chi-square (for binominal data), and Mann-Whitney U-test (for non-normally distributed data) will be used to examine baseline equivalence and attrition between groups. Due to the multi-level and hierarchical nature of the data, mixed effects regression will be used to examine intervention by time interaction effects. To account for intracluster variance within States or schools, intervention effects will primarily be examined using hierarchical linear modelling (HLM) for normally distributed data and hierarchical generalized linear modelling using a Poisson distribution for count data. Outcome variables will be centred at post-test to allow for comparisons between groups immediately after the intervention, and growth terms will be analysed to determine the magnitude of the follow-up effects. Analyses will be conducted using the program Stata. If unconditional models reveal that less than 10% of systematic variance exists at the between State or between school level for any outcome variable, HLM will be abandoned and single-level analyses will be used [67]. For these variables, ANCOVAs utilising the SPSS GLM procedure will be conducted to account for any baseline differences that might exist between groups. For multiple comparisons Bonferroni adjustments will be made. Effect sizes, odds ratios and 95% confidence intervals will also be calculated.

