### Strengths and limitations

The preventative focus of the CSC study on comorbid substance use and mental health symptoms in young people is a key strength of the study. To date, school prevention programs for anxiety, depression and substance use have mostly been designed to target one disorder at a time, rather than targeting all these common disorders. The development and evaluation of a combined prevention approach to mental health and substance use problems is a critical step in acknowledging the comorbidity of these problems, including common antecedents, as well as influencing policy to improve mental health and wellbeing.

The CSC intervention has been designed to overcome many obstacles and limitations of current school-based preventative programs. First, the program has been specifically designed to link with the curriculum, and is thereby potentially practical, acceptable, and scalable to all schools in Australia. Furthermore, implementation issues that have hindered previous school-based programs have been addressed through the use of innovative online delivery methods, which are designed to increase program fidelity and increase student engagement.

Finally, the study has been powered to allow for comparisons between all four of the intervention conditions, both nationally and within each of the three States for effect sizes as low as .15. Such a large sample will allow for the detection of even small differences between groups. This will enable the investigators to establish the efficacy of the combined program over and above the stand-alone programs, as well as normative substance use and mental health education in Physical Health and Education classes as usual.

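### Plain Bonferroni is fixed for multiple comparisons, although Holm's step-down version gives the same family-wise guarantee and never rejects less; the gain is mainly in the within-State comparisons

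*Protocol article*

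**What the plan says.** The only multiplicity rule in the protocol article is one sentence near the end of Statistical analysis: "For multiple comparisons Bonferroni adjustments will be made". It names no step-down version and does not say which comparisons form the family. The next sentence plans effect sizes, odds ratios and 95% confidence intervals, and does not describe the intervals as adjusted.

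Three other places bear on the point:

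- Objectives of the CSC study names three comparators for the combined programme. It begins "It is hypothesised that the CSC program will be more effective than; (1) school-based Health and Physical Education as usual" and goes on to the substance use programme alone and the mental health programme alone.
- Sample size calculations sets the design within each State: "six schools (with at least 100 students) in each of the four intervention groups are required per state". The power statement is "This achieves 80 per cent power to detect a standardized between-group mean difference of 0.15 (p = 0.05"), and it refers to a difference "in outcomes at the end of the trial with seven measurement occasions".
- Strengths and limitations says the trial is powered for comparisons between all four conditions, "both nationally and within each of the three States for effect sizes as low as .15".

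**The concern.** Single-step Bonferroni with three comparisons holds every p-value to 0.05/3 = 0.0167. Holm holds the smallest to 0.0167, the next to 0.05/2 = 0.025 and the largest to 0.05, and stops at the first failure. Its first step is the Bonferroni test and its later steps are easier, so it rejects everything that Bonferroni rejects and sometimes more. Both guarantee family-wise error of at most 0.05 whatever the dependence between the tests, provided that each p-value is itself valid.

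For example, p-values of 0.010, 0.020 and 0.040 give one significant comparison under Bonferroni (only 0.010 is below 0.0167). They give three under Holm (0.010 < 0.0167, 0.020 < 0.025, 0.040 < 0.05).

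At stake is power that the chosen procedure gives up with no stronger error guarantee in return. It counts most where the plan has least to spare, in the comparisons within one State.

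**Working it through.** **The plan's own figure.** The stated power within a State is 80% for 0.15 SD at p = 0.05, with 6 × 100 = 600 students per group. It cannot be confirmed or refuted, because the article gives neither the intracluster correlation nor the within-student correlation. A plain end-of-trial comparison of 600 against 600 gives 73.8% at an intracluster correlation of 0, 56.5% at 0.005 and 45.3% at 0.01. A linear-slope calculation over seven occasions gives 78.2% at a within-student correlation of 0.3 and 84.1% at 0.4. The 80% is therefore taken as stated. Which procedure is more powerful does not depend on it.

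**Inputs**
- From the plan: 80% power, 0.15 SD, alpha 0.05, four equal groups, three comparators.
- Assumed: two-sided tests; family = the three CSC contrasts on one outcome; true difference 0.15 SD in each.
- Correlation between two contrasts that share the CSC group, with equal groups: σ²/(2σ²) = 0.5.

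**Noncentrality within a State:** 1.960 + 0.842 = 2.802.

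**Critical values:** Bonferroni 2.394 for all three. Holm 2.394, 2.241 and 1.960 for the largest, middle and smallest statistic.

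**Bonferroni, one comparison:** Φ(2.802 − 2.394) = Φ(0.408) = 65.8%, down from 80%.

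**Remaining figures:** trivariate normal with correlation 0.5. Holm was simulated with 3 to 4 million draws.

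| Setting | Measure | Bonferroni | Holm |
|---|---|---|---|
| Within a State, 0.15 SD | average per comparison | 65.8% | 73.5% |
| Within a State, 0.15 SD | all three significant | 41.7% | 59.2% |
| Within a State, family of six pairs | all three CSC contrasts significant | 31.3% | 37.1% |
| National, 0.15 SD | all three significant | 98.1% | 99.4% |

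The six-pair row takes the other three groups as equal to one another. The national row takes three times the within-State information, so the noncentrality is 2.802 × √3 = 4.85.

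**A smaller national effect, for illustration only.** A difference of 0.10 SD is not a figure from the protocol. It gives 2.802 × √3 × 0.10/0.15 = 3.235. All three are then significant in 61.0% of trials with Bonferroni and 76.6% with Holm. Per comparison the figures are 80.0% and 86.4%.

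**Sensitivity of the within-State all-three figures (Bonferroni against Holm)**
- One-sided tests: 39.5% against 58.6%.
- t reference with 20 df: 40.9% against 59.5%; with 10 df: 40.0% against 59.4%.
- Difference from usual education twice as large: 50.6% against 67.7%.

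**Check of error control (simulated family-wise error, Bonferroni against Holm)**
- All three nulls true: 4.4% for both.
- One real effect, two nulls: 3.1% against 4.0%.
- Two real effects, one null: 1.7% against 3.5%.
- Two very large effects, one null: 1.7% against 5.0%.

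The guarantee is the same. The realised error rates differ once some effects are real, because Holm uses error allowance that Bonferroni leaves unspent.

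**The case against.** The strongest case on the other side is that nothing here is wrong. Bonferroni is valid and familiar, has simple matching intervals, and is stated in one sentence of a condensed article. Most of that stands, and it limits the point to efficiency. The argument from intervals is weaker, because the planned 95% intervals are not described as adjusted.

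A reader might infer that the trial's main claim, CSC better than all three comparators, has only a 42% chance of success where Holm would give 59%. The documents do not support that, for three reasons.

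- **Level.** Sample size calculations assigns the test of CSC against the other groups to the full sample of 84 schools, with within-State comparisons as a further powered aim. The objectives contain no State-level hypothesis. Nationally at the plan's own 0.15 SD the gain is about 1 point.
- **Joint success.** The objectives list three comparators but do not say that all must be significant together. The statement "This will enable the investigators to establish the efficacy of the combined program over and above the stand-alone programs" does not set such a rule either. For separate claims the within-State gain is 73.5 − 65.8 = 7.7 points.
- **Family.** It is not defined. Strengths and limitations speaks of comparisons between all four conditions, which is six pairs, and there the all-three gain is 37.1 − 31.3 = 5.8 points.

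The sentence also follows directly on the ANCOVA fallback, so its scope is slightly ambiguous. It is worded generally, and no other multiplicity rule is given.

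It may also be said that a claim of superiority over all three needs no adjustment at all, since testing each at 0.05 already controls the error of that joint claim (61.1% within a State). That is correct for a declared joint claim, but the plan declares none, and the rule does not sit beside Holm. With p = 0.03 in all three comparisons, Holm rejects none (0.03 > 0.0167) while the joint rule declares all three.

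**Conclusion.** The point holds as a cheap improvement. Holm is at least as powerful as plain Bonferroni under the same family-wise guarantee, and that ranking needs no assumption about clustering, effect size or family.

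The size does need assumptions: the stated 80% at face value, equal groups, equal true differences of 0.15 SD, and a family of three contrasts on one outcome. On these, the within-State gain is about 8 points per comparison and about 17 points for all three together. It is about 6 points on the all-three measure with six pairs, and about 1 point nationally at 0.15 SD. The change is worth making mainly for the within-State comparisons, or if true effects are smaller than the design effect. It is not evidence that the national comparison is poorly served or that Bonferroni is invalid.

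**What to change.** Replace the sentence with: 'For multiple comparisons, p-values will be adjusted by the Holm step-down procedure.' Do not pair it with a rule that declares superiority over all three comparators from unadjusted tests at 0.05, because the two rules can give opposite answers on the same data.

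The change costs one sentence and no schools, students or data. It should be made before the outcome data are analysed, so that the choice cannot appear to follow the results. The small downside is that Holm has no simple matching simultaneous confidence intervals. Report the planned 95% intervals as unadjusted and label them so, or add Bonferroni intervals beside them.

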## Discussion

The present study protocol presents the design of a cluster RCT to evaluate the effectiveness of the CSC intervention; an integrated universal program to prevent alcohol and cannabis use and symptoms of anxiety and depression among adolescents. The primary aims of the CSC study are to evaluate the effectiveness of the CSC intervention compared to universal prevention programs for substance use and anxiety/depression when delivered alone and compared to school-based Health and Physical Education as usual in relation to; a) reducing the uptake and harmful use of alcohol and other drugs, b) reducing rates of anxiety and depression, and c) increasing mental health and substance use related knowledge.

### Strengths and limitations

The preventative focus of the CSC study on comorbid substance use and mental health symptoms in young people is a key strength of the study. To date, school prevention programs for anxiety, depression and substance use have mostly been designed to target one disorder at a time, rather than targeting all these common disorders. The development and evaluation of a combined prevention approach to mental health and substance use problems is a critical step in acknowledging the comorbidity of these problems, including common antecedents, as well as influencing policy to improve mental health and wellbeing.

The CSC intervention has been designed to overcome many obstacles and limitations of current school-based preventative programs. First, the program has been specifically designed to link with the curriculum, and is thereby potentially practical, acceptable, and scalable to all schools in Australia. Furthermore, implementation issues that have hindered previous school-based programs have been addressed through the use of innovative online delivery methods, which are designed to increase program fidelity and increase student engagement.

Finally, the study has been powered to allow for comparisons between all four of the intervention conditions, both nationally and within each of the three States for effect sizes as low as .15. Such a large sample will allow for the detection of even small differences between groups. This will enable the investigators to establish the efficacy of the combined program over and above the stand-alone programs, as well as normative substance use and mental health education in Physical Health and Education classes as usual.

One limitation of the study is the inclusion of participant self-report measurement for the primary outcomes of substance use and mental health symptoms. The use of self-report measures introduces the possibility of over or under reporting by participants. However, self-report measures have demonstrated excellent discriminant [68] and predictive [69] validity in relation to substance related symptoms [53]. Self-report remains the most practical and popular method of assessment of substance use and mental health in young people within school settings. There are also currently no other feasible alternatives for data collection on substance use and mental health in these settings, as biological or observational measures would not be appropriate for such a large sample in the early stages of substance use initiation and mental health symptoms [70]. In order to maximise the accuracy of students’ self-report data, the investigators will employ the following strategies: visual prompts in the form of standard drink charts, blind administration of any paper and pencil assessments within schools, and a strong emphasis on anonymity and confidentiality, with a special emphasis placed in the fact that schools and parents will not be given access to individual participants’ data.

## Conclusion

Research has highlighted the comorbidity of anxiety, depressive and substance use disorders, yet there are no existing prevention programs which adopt a combined approach to prevent and reduce symptoms associated with these common disorders. Furthermore, while a number of preventative programs for substance use and mental health symptoms are available, many yield minimal effect sizes, are not universally feasible and do not embody effective implementation strategies. The CSC study will be the first trial, internationally, to test a combined prevention model, whilst addressing the aforementioned limitations identified in current preventive programs.

The CSC intervention has the potential to reduce substance use, as well as reduce rates of anxiety and depression at higher levels than either; a) separate substance use and mental health programs and, b) traditional classroom Health and Physical Education. Importantly, this study offers the potential for a paradigm shift, such that future preventive programs and research adopts a combined approach into understanding comorbid substance use and mental health disorders.

### Ethics approval number

Ethics approval has been granted by the UNSW Human Research Ethics Committee (HC13073).

